## Abstract

**Background:**

Heart failure (HF) is a highly prevalent chronic disease, for which there is no cure available. Therefore, improving disease management is crucial, with mobile health (mHealth) being a promising technology. The aim of the HeartMan study is to evaluate the effect of a personal mHealth system on top of standard care on disease management and health-related quality of life (HRQoL) in HF.

**Methods:**

HeartMan is a randomized controlled 1:2 (control:intervention) proof-of-concept trial, which will enrol 120 stable ambulatory HF patients with reduced ejection fraction across two European countries. Participants in the intervention group are equipped with a multi-monitoring health platform with the HeartMan wristband sensor as the main component. HeartMan provides guidance through a decision support system on four domains of disease management (exercise, nutrition, medication adherence and mental support), adapted to the patient’s medical and psychological profile. The primary endpoint of the study is improvement in self-care and HRQoL after a six-months intervention. Secondary endpoints are the effects of HeartMan on: behavioural outcomes, illness perception, clinical outcomes and mental state.

**Discussion:**

HeartMan is technologically the most innovative HF self-management support system to date. This trial will provide evidence whether modern mHealth technology, when used to its full extent, can improve HRQoL in HF.

**Trial registration:**

This trial has been registered on https://clinicaltrials.gov/ct2/show/NCT03497871, on April 13 2018 with registration number NCT03497871.

## Background

About 1–2% of people in the western world suffer from heart failure (HF) [1]. Although treatment improvements have decreased the number of hospitalizations and deaths due to HF, the burden remains high with half of the HF patients being expected to die within five years after diagnosis, and HF being the most frequent cause of hospitalization in people aged over 65 [2].

Since there is presently no cure available, a better management of HF is crucial. Proper disease management may relieve symptoms, prevent hospitalization or improve survival, but may also affect the patient’s health-related quality of life (HRQoL). The European Society of Cardiology (ESC) Task Force produced guidelines for the diagnosis and management of HF, intended to be used by clinical practitioners [3]. However, previous studies consistently show an insufficient uptake of these guidelines in clinical practice [4]. Of particular concern is the poor implementation of exercise guidelines [5]: participation rates of HF patients in cardiac rehabilitation are generally below 20% in Europe [6]. This calls for action to develop strategies to give appropriate and effective personalized lifestyle advice to HF patients.

A promising technology for improving disease management in HF may be mobile health (mHealth), which encompasses the use of mobile devices as a support to clinical practice. mHealth has already been implemented in HF patients to provide regular follow-up and physiological monitoring, to ensure safety and to detect complications [7]. In addition, it may be a tool to deliver education and support patients regarding self-monitoring and self-management. However, evidence on the effectiveness of this approach in HF patients has been diverse. A recent meta-analysis suggests clinical benefits on all-cause mortality and heart failure related hospitalisations [8], but large clinical trials did not show any effect on readmission or death [9, 10]. However, the BEAT-HF trial found despite the absence of reduced rehospitalization or mortality, an improvement in HRQoL [11].

HRQoL and perceived health status, both patient-reported outcomes (PROs), have increasingly been recognized as outcomes of interest in HF and coronary patients [12, 13]. PROs are not surrogates for harder endpoints such as mortality, but rather represent independent outcomes [14]. Nevertheless, some studies report that HRQoL and health status may be predictive of clinical events in HF [15, 16], suggesting a relation between both types of outcome. These findings indicate that patients’ perceptions of worsening symptoms might carry vital prognostic information, and should be implemented in trials evaluating disease management.

An aspect that has been largely ignored in mHealth trials is the psychological aspect that is necessary to start changing behaviour and to cope with HF symptoms. Psychological interventions such as cognitive behavioural therapy and mindfulness exercises have already been shown to be successful in changing lifestyle behaviour [17, 18] and to significantly reduce anxiety, depression and clinical symptoms which are common in HF patients [19]. Therefore, implementing psychological interventions in mHealth technology may offer an added value.

This paper presents the study protocol of HeartMan (*Personal Decision Support System For Heart Failure Management)* which aims to develop a personal health system to improve disease management and HRQoL in HF. In this system, patients’ monitoring is focused on their physical condition and psychological state. This data is integrated into a decision support system (DSS), which is an information system supporting complex decision making processes. In HeartMan, the DSS suggests the most appropriate intervention (including exercise, nutrition, medication and mental support) to modify and manage the patient’s lifestyle, adapted to his psychological profile in order to increase adherence to the medical advice.

## Study design

### Design

HeartMan is a randomized controlled 1:2 (control:intervention) proof-of-concept trial, being conducted across two countries (Belgium and Italy) to compare standard care in HF with the addition of a personal mHealth system on top of standard care. In each country 60 patients are enrolled for a six-month period. Hence 40 patients in total are included in the control group and 80 in the intervention group.

### Study objectives and outcome measures

The overall objective of HeartMan is to improve disease management, resulting in an improvement in HRQoL after a 6 months intervention period.

Secondary objectives are the effects of HeartMan on behavioural outcomes, illness perception and clinical outcomes which may impact disease management and HRQoL. Additional secondary aims encompass the effects of psychological interventions within HeartMan and a user-friendly design of the HeartMan system.

Primary and secondary outcome measures, which are assessed in the intervention and control group, are listed below. These measures are collected at start and end of the study, unless otherwise stated.

#### Primary objective

The primary endpoint is the self-reported improvement in self-care and HRQoL, measured by the Self-care of Heart Failure Index [20] and Minnesota Living with Heart Failure Questionnaire [21]

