##### Baseline visit

After patients have signed the informed consent form stating their willingness to be randomized, a baseline assessment is planned in the hospital maximum 20 weeks prior to the start of the trial. During this visit, all patients perform a 6MWT, which is in line with the recommendations of the Heart Failure Association of the ESC [5] to evaluate one’s exercise capacity in case cardiopulmonary exercise testing (CPET) is not available.

In addition, every participant receives a self-administered questionnaire package which is filled in during the baseline assessment. These questionnaires have previously been described in the study outcome measures section and details are listed in Table 1*.*

**Table 1 Tab1:** Overview of the questionnaire package

Questionnaire	Description	Number of items	Subscales
Self – care of Heart Failure Index [20]	Self-care	22	Self-care behavior, self-care management, self-care confidence, and symptom perception
Minnesota Living with Heart Failure Questionnaire [21]	Health – related quality of life	21	Physical, socio-economic, and emotional/psychological aspects
Brief Illness Perception Questionnaire [24]	Illness perception	9	Cognitive representation, emotional representation, illness comprehensibility, and perceived cause of illness
Sexual Adjustment Scale [22] (subscale of the Psychosocial Adjustment Scale)	Sexual activity	6	Relationship and sexuality
Needs for Sexual Counseling Scale in Chronic Heart Failure [23]	Sexual activity	21	Symptoms, medication and information, relaxation, relationship, and psychological factors
State Trait Anxiety Inventory [26]	Anxiety	40	State anxiety scale (s-anxiety) and trait anxiety scale (t-anxiety)
Beck Depression Inventory II [27]	Depression	21	Depression and anxiety
Unified theory of acceptance and use of technology questionnaire [28]	User expectations and user experience	37	/
Self – composed questionnaire on nutritional behavior	Nutritional behavior	24	Drinking behavior and eating behavior
Self – composed questionnaire on nutritional knowledge	Nutritional knowledge	12 (14: patients with diabetes)	Knowledge about heart failure (and diabetes) nutrition

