#### Statistical analysis

The main analysis of primary and secondary endpoints will be based on the Intention-To-Treat principle, i.e. including all patients in the analysis who did not drop out within the first 4 weeks of the trial. In order to assess the clinical effect of the HeartMan intervention on the different outcomes, an additional per-protocol analysis will be performed in patients who adhere to the treatment plan for at least 50%. Based on these results, a dose-response analysis will be conducted to verify the relation between the level of adherence and intervention effects.

Prior to each analysis, distribution of the variables will be checked in order to choose correct statistical tests and identify outliers. In all analyses, *p* values < 0.05 will be considered to be statistically significant.

Effects of the proof-of-concept trial will be assessed by analysing baseline and end-of-investigation data between and among treatment groups. The primary endpoint of the HeartMan project is the self-reported improvement in HRQoL. First, T-tests or its non-parametric variant and chi-square tests will be used to compare the characteristics between the groups. Next, in order to assess the effect of the intervention among the different groups, a repeated measures design with time*group interaction effect will be chosen. A similar statistical approach will be performed for the secondary analyses.

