## Discussion

HeartMan aims to provide appropriate and comprehensive guidance on different domains of disease management in HF, tailored to the patient’s medical and psychological profile. This approach is intended to have a positive impact on HRQoL, which is the primary outcome of this trial.

The focus on HRQoL as a primary outcome instead of targeting hard outcomes such as mortality and hospitalization is one of the innovative approaches in comparison with previous mHealth studies. [8–10] HRQoL has gained more attention lately, often as a secondary outcome [11], although it also becomes more prominent as a primary outcome in recent studies [13].

Results on the effectiveness of mHealth technologies are rather mixed. Plausible reasons may be the focus on a single intervention modality (e.g. education) or a lack of patient’s adherence to technology. In HeartMan, the combination of different intervention modalities, adapted to the individual patient’s physical and psychological condition, is a unique approach, which makes HeartMan stand out from related projects. Another aspect that may increase the likelihood of successful adherence is the involvement of patients in the designing process of HeartMan, making it more adapted to the patient’s daily life.

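### The primary endpoint is self-care and HRQoL in two places and HRQoL alone in two others, so what counts as success depends on which section is followed

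*Protocol article*

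**What the plan says.** Four places in the protocol article define the primary endpoint, and they divide two against two.

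- **Abstract, Methods:** "The primary endpoint of the study is improvement in self-care and HRQoL after a six-months intervention".
- **Primary objective:** "The primary endpoint is the self-reported improvement in self-care and HRQoL, measured by the Self-care of Heart Failure Index"; the sentence goes on to name the MLHFQ as the second instrument.
- **Statistical analysis:** "The primary endpoint of the HeartMan project is the self-reported improvement in HRQoL".
- **Discussion:** "This approach is intended to have a positive impact on HRQoL, which is the primary outcome of this trial".

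The section on study objectives gives the aim as: "The overall objective of HeartMan is to improve disease management, resulting in an improvement in HRQoL after a 6 months intervention period". The list under Secondary objectives covers behaviour, illness perception, exercise tolerance, anxiety and depression, and user experience. It does not include the SCHFI.

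For testing, the Statistical analysis section says that "a repeated measures design with time*group interaction effect will be chosen", and for all analyses that p "values < 0.05 will be considered to be statistically significant". It gives no rule for combining or ordering the two questionnaires.

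**The concern.** The primary endpoint decides whether a trial has met its aim. Here the section that defines the endpoint has two constructs on two instruments, while the section that analyses it has one.

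Suppose the MLHFQ comparison is null and the SCHFI comparison has p < 0.05. The Statistical analysis section makes the trial negative. Under the Primary objective section, the trial has a significant result on one of its two primary instruments, and nothing says whether that is enough. The reverse case, a positive MLHFQ and a null SCHFI, is a success under the first section. Under the second it is a failure if both are required.

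Both definitions are published, so the choice between them could be made after the results are seen. Because the secondary list omits the SCHFI, the HRQoL-only definition also leaves self-care with no status at all.

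**Working it through.** **Does another section settle the matter?**

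| Section | Self-care primary? | HRQoL primary? |
|---|---|---|
| Abstract, Methods | yes | yes |
| Primary objective | yes (SCHFI) | yes (MLHFQ) |
| Statistical analysis | not named | yes |
| Discussion | not named | yes |
| Secondary objectives | SCHFI not listed | not listed |

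The overall objective puts disease management first and HRQoL as its result. That leans towards HRQoL but is compatible with either definition. The sample size rests on average daily awake heart rate, so it does not show which questionnaire was meant to carry the trial. There is no stated figure for either questionnaire to reproduce.

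**Type I error under each reading**

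Inputs: α = 0.05 per test (Statistical analysis). Two-sided testing is an assumption, since sidedness is not stated. The correlation ρ between the two test statistics is also an assumption, with the range shown.

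1. *HRQoL alone:* one test, error 0.05.
2. *Both required:* if only one null is true, the error cannot exceed that test's 0.05, so the maximum is 0.05. If both nulls are true and the tests independent, it is 0.05 × 0.05 = 0.0025.
3. *Either accepted, both nulls true, independent:* 1 − (1 − 0.05)² = 1 − 0.9025 = 0.0975.
4. *Either accepted, correlated:* 1 − P(|Z₁| < 1.96 and |Z₂| < 1.96), with (Z₁, Z₂) bivariate normal. The both-significant column is 0.05 + 0.05 minus the either column.

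| ρ | Either significant | Both significant (both nulls true) |
|---|---|---|
| 0 | 0.0975 | 0.0025 |
| 0.3 | 0.0951 | 0.0049 |
| 0.5 | 0.0907 | 0.0093 |
| 0.7 | 0.0835 | 0.0165 |

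**Power, as illustration only**

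Requiring both can never give more power than the weaker endpoint has alone. If each questionnaire had 90% power at α = 0.05, the power for both would be 0.90 × 0.90 = 0.81 at ρ = 0 and 0.847 at ρ = 0.7. At α = 0.025, the first step of Holm, each endpoint's power would be Φ(1.960 + 1.282 − 2.241) = Φ(1.00) = 0.84. The 90% is borrowed: the article states it for heart rate and gives no power for either questionnaire.

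**The case against.** The best defence has four parts.

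- **No inflation in the text itself.** The endpoint section joins the two constructs with *and*. The readings closest to the wording are HRQoL alone and both required, and both hold the error at 5% or less. This stands. A reader might infer that the plan has an uncontrolled error rate of nearly 10%, but that needs an either-is-enough rule that appears nowhere.
- **Subscales.** Table 1 lists four SCHFI subscales ("Self-care behavior, self-care management, self-care confidence, and symptom perception"). A reader might count these with the MLHFQ as five tests and obtain 1 − 0.95⁵ = 0.226. The article does not support this. Table 1 describes the questionnaire package, gives subscales for most instruments including the MLHFQ, and makes none of them an endpoint. Choice of score and handling of multiplicity may properly sit in an analysis plan that is not shown.
- **Intent is recoverable.** The overall objective, the analysis section and the Discussion all centre on HRQoL. This makes HRQoL the likelier intention, but it does not withdraw the explicit definition in the Primary objective section.
- **Proof of concept.** The trial is called preliminary, which lowers the stakes of strict error control. The Discussion nonetheless offers the results as a basis for larger studies, so a clear success criterion still matters.

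None of these makes the two definitions agree. An unseen analysis plan could add detail, but the published text would still contain both.

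**Conclusion.** The point holds as an inconsistency in the definition of the primary endpoint. It is a contradiction in current text, not missing detail or the effect of condensing a longer protocol.

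Its size depends on the reading:
- HRQoL alone: type I error 5%.
- Both required: at most 5%, with lower power than a single endpoint in general.
- Either accepted: about 8.3% (ρ = 0.7) to 9.8% (ρ = 0).

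These figures assume two-sided tests. The last is conditional on a rule that the article does not state. The power loss under the both-required reading cannot be quantified for this trial, because the stated 90% concerns heart rate. Nor do the analysis section and Discussion specify an MLHFQ total score; they say only HRQoL.

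**What to change.** Before outcome data are examined, give one definition of the primary endpoint in the Abstract, Primary objective, Statistical analysis and Discussion sections.

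**Option closest to the analysis section.** Make HRQoL, measured by one pre-named MLHFQ score, the single primary endpoint. The total score is a natural choice, but it is a proposal here and not something the article states. List one pre-named SCHFI score as the first key secondary endpoint, tested at 5% only if the primary is significant. This fixed sequence keeps the error at 5% across the two.

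**If both stay primary.** State either that both must be significant at 5%, or that Holm is applied across the two pre-named scores. The first fits the *and* in the endpoint section and costs power. The second allows a claim on one questionnaire but starts at 2.5%.

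**Cost.** No new patients, visits or measurements are needed. Under the single-primary option, self-care can be claimed only after HRQoL succeeds. The trial is registered and already enrolling, and two sections now call self-care primary. The change should therefore be dated and documented as a clarification in the protocol and the registry, not made as a silent edit.

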#### Secondary objectives

Effect of HeartMan on behavioural outcomes, which are:Adherence to dietary recommendations, measured by a self-composed questionnaire on nutritional knowledge and eating behaviourActivity behaviour, daily measured by the number of calories (via an accelerometer in the HeartMan wristband sensor)Medication adherence by questioning the patient on their medication intake on a weekly basisSexual activity, assessed with the Sexual Adjustment Scale [22] and Needs for Sexual Counselling Scale in chronic HF [23]Effect of HeartMan on illness perception, evaluated with the Brief Illness Perception Questionnaire [24]Effect of HeartMan on exercise tolerance, measured by:Change in resting heart rate and heart rate during exerciseDistance obtained at the six–minute walking test (6MWT) [25]Effect of psychological interventions in HeartMan – cognitive behavioural therapy and mindfulness exercises – on anxiety and depressive feelings, measured with State Trait Anxiety Inventory [26] and the Beck Depression Inventory II [27]Evaluation of the user experience of HeartMan to assess the expectations towards the system and the patient’s experiences (only measured in the intervention group), evaluated with the Unified Theory of Acceptance and Use of Technology questionnaire, [28] adapted to the objectives of the HeartMan system and to the population of elderly users [29]

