### Intervention equipment

Participants randomized to the intervention group are equipped with a multi-monitoring health platform able to monitor, process and fuse physio-psychological and behavioural data. The main component of the trial equipment is the HeartMan wristband sensor developed by BITTIUM (Oulo, Finland). This is an ambulatory recorder and transmitter for heart rate, heart rate variability, galvanic skin response, skin temperature, respiration rate and motion. This wristband has Bluetooth communication, recording function, display, haptic interface and the ability to synchronize with other external devices. Apart from the HeartMan wristband sensor, the equipment consists of registered and commercially available devices including a digital bathroom scale (ADE, Model Silje BE1303), upper arm blood pressure monitor (A&D Medical, Model Number UA-611) and a pill box organizer (PuTwo, 7-Day AM/PM Night Reminder Medi-Planner). Furthermore, a smartphone (Nokia 6 TA_1021) with HeartMan app installed is provided for the duration of the trial.

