Exercise	Endurance exercise	*-* Assessment of physical capacity: cyclo-ergometry (if available) and 6MWT *-* Differentiation based on baseline physical capacity level (low level: cyclo-ergometry < 1 W/kg or 6MWT < 300 m vs. normal level: ≥1 W/kg or 6MWT ≥300 m) *-* Individual exercise program via the application: ○ Frequency: 2–5 times per week ○ Intensity: HR rest + 40–70% HRR or RPE 10–14/20 ○ Time: 10-40 min ○ Type: cycling, walking, steps *-* Individual progress: ○ Increase in frequency or time after a predefined number of weeks (after patient’s approval) ○ Increase in intensity if following criteria are met: • Adherence to exercise therapy > 60% of training sessions • Not overshooting the target heart rate in 80% of the training sessions • Patient’s subjective opinion of exercise intensity: ‘no discomfort’ in 80% of the training sessions • After at least 8 weeks of exercise training
	Resistance exercise	*-* Differentiation based on baseline physical capacity level *-* Individual exercise program via the application: ○ Frequency: 2–3 times per week ○ Intensity: 60–70% 1Repetition maximum ○ Time: 1–2 sets per day ○ Type: dynamic upper and lower limb exercises, with no or light weights *-* Individual progress: ○ Increase in frequency or time after a predefined number of weeks (after patient’s approval) ○ Increase in intensity (from no weights to light weights) after a predefined number of weeks (after patient’s approval)
Medication intake	Weekly pill organizer	*-* Passive pill dispenser, with personalized reminder function in HeartMan application: ○ Guidance to prepare medication once per week ○ Daily personalized notifications to remind the patient to take his medication at the right time *-* Assessment of medication adherence by a weekly question whether the patient has taken the recommended medication or not
Appointments		*-* Personalized reminder function in HeartMan application 1 day before the appointment (only upon the patient’s request)
Mental support	Cognitive behavioral therapy	*-* Patient profiling: adaption of the communication according to the psychological profile (anxious, depressed or low motivation) in order to increase adherence to lifestyle interventions
	Mindfulness exercises	*-* Mindfulness exercises are offered to the patient on a daily basis, adapted to the patient’s profile (anxious, depressed or motivated). *-* Different types of exercises: ○ Listening ○ Focusing ○ Awareness ○ Games

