### Handling missing data

A great effort will be made to have complete data on outcome measures and to use all obtained information. For early drop-out within 4 weeks after starting the intervention, novel candidates will be foreseen.

For those who drop out in a later phase, efforts will be made to perform the end-of-study examination and if not feasible, these will be considered as missing data. In the case of missing data, some of the outcome measures (e.g. heart rate or blood pressure) can be retrieved through data from the HeartMan system, using the Last Observation Carried Forward (LOCF) principle.

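### Activity is measured only by a wristband described for the intervention arm, medication adherence has no described control-arm source, and the device-based LOCF rule can fill values in one arm only

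*Protocol article*

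**What the plan says.** Under Study objectives and outcome measures, the article states: "Primary and secondary outcome measures, which are assessed in the intervention and control group, are listed below". Collection is at the start and end of the study unless otherwise stated.

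Under Secondary objectives, activity behaviour is "daily measured by the number of calories (via an accelerometer in the HeartMan wristband". Medication adherence is obtained by weekly questioning, with no route named. Resting and exercise heart rate are listed under exercise tolerance, with no device named. User experience is the only outcome marked as measured in the intervention arm alone.

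Under Intervention equipment: "Participants randomized to the intervention group are equipped with a multi-monitoring health platform". The wristband is the main component of that platform. Under Baseline visit, randomisation follows the baseline assessment. Under Intervention, the tool is introduced to the intervention group at a home visit.

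Table 2, which lists the HeartMan intervention components, includes under medication intake: "Assessment of medication adherence by a weekly question whether the patient has taken the recommended medication or not". Table 1, the questionnaire package completed by every participant, has no medication-adherence item.

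The Statistical analysis section specifies a repeated-measures design with a time-by-group interaction and adds: "A similar statistical approach will be performed for the secondary analyses". Handling missing data says that some outcomes, with heart rate and blood pressure as examples, "can be retrieved through data from the HeartMan system, using the Last Observation Carried Forward (LOCF) principle".

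**The concern.** A time-by-group test needs the same measurement in both arms at both times. If an outcome is produced by the intervention's own equipment, the control arm has nothing to compare and the baseline cannot precede allocation. What remains is a trend over time within the intervention arm. That trend cannot be separated from natural course, regression to the mean or the effect of wearing a monitor. The article nevertheless lists activity and medication adherence as outcomes on which HeartMan has an effect.

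The missing-data rule raises a related problem. A value carried forward from the HeartMan system can be supplied for an intervention patient who misses the final visit, but never for a control. The two arms would then be summarised by different rules: one by visit values plus home-device values from before the patient stopped, the other by visit values alone.

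**Working it through.** The plan gives no figure for this point, so there is none to reproduce. The check is mainly of which data each arm can supply.

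**Activity.** The Design section gives 40 control and 80 intervention patients. The interaction estimates

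(intervention end − intervention baseline) − (control end − control baseline).

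- Intervention, on study: wristband calories, up to 80 of 80 patients.
- Intervention, before randomisation: none described, because the tool is introduced after allocation.
- Control, baseline: none described.
- Control, end: none described, 0 of 40.

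Three of the four means have no described source, so the interaction is not estimable. Even a simple comparison at the end of the study has an empty control arm. No section gives controls a wristband or another activity measure.

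**Medication adherence.** The outcome definition names no device. The one operational description is in Table 2, and the text on intervention components also treats weekly tracking as part of the intervention. The Table 1 package does not contain the question. The article therefore describes no control-arm source, but it does not exclude one, since a control patient can be asked without any equipment.

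**Heart rate.** The outcome definition names no device. The wristband entry in Table 3 concerns alert notifications. Both arms attend the baseline and end-of-study hospital visits and perform the six-minute walking test there, so comparable heart-rate readings are possible in both arms.

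**LOCF.** Let d be the proportion in each arm who miss the final visit. Fillable values are at most 80 × d in the intervention arm and 0 of the 40 × d missing in the control arm. The article states no dropout rate. Its step from 90 to 120 patients implies an allowance of 1 − 90/120 = 25%. Taking 10% to 25% as an assumed range, equal in both arms:

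| d | Intervention values fillable | Control values fillable |
|---|---|---|
| 10% | up to 80 × 0.10 = 8 | 0 of 40 × 0.10 = 4 |
| 25% | up to 80 × 0.25 = 20 | 0 of 40 × 0.25 = 10 |

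If carried values differ from the unseen visit values by g on average, the intervention mean moves by d × g, with no matching movement in the control arm. For an assumed g of 2 to 8 bpm in absolute size:

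- d = 10%: 0.10 × 2 = 0.2 to 0.10 × 8 = 0.8 bpm.
- d = 25%: 0.25 × 2 = 0.5 to 0.25 × 8 = 2.0 bpm.

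The documents give neither the size nor the sign of g, so this shows how the asymmetry works and is not an estimate of bias.

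**The case against.** The best defence is that this is a condensed article. It says plainly that outcomes are assessed in both arms, and the full protocol may describe how controls are followed. For medication adherence this carries weight. A reader might infer that no control has adherence data, but the article does not show that: the outcome is defined by questioning the patient, and Table 2 describes the content of the intervention, not the follow-up of controls. What stands is only that no comparable control-arm source is described.

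The defence also succeeds for heart rate as an outcome. A reader might infer that heart rate too lacks a comparator. The documents do not support that, because visit readings are possible in both arms.

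The LOCF rule is worded as an option. Drop-outs within four weeks are to be replaced, and efforts are planned to hold the final examination for later ones, so the number of filled values may be well below the upper limits above. It is also tempting to express a possible shift as a share of the 5.8 bpm in the sample size section. That would mix quantities: 5.8 bpm refers to average daily awake heart rate, whereas the listed outcome is resting and exercise heart rate.

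The defence does not reach activity. Its measuring instrument is named in the outcome definition and described only as intervention equipment, and the article marks a single-arm outcome elsewhere when it means one. Nor does it remove the asymmetry of the LOCF rule, which needs no assumption about numbers.

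**Conclusion.** The point holds for secondary outcomes, with different strength by part.

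- **Activity:** a direct contradiction. The two-arm assessment and the time-by-group analysis cannot be run with 0 of 40 controls measured and no pre-randomisation baseline. This assumes that controls receive no wristband, which is what every description of the equipment implies.
- **Medication adherence:** a gap. No comparable control-arm source is described, although one is possible.
- **LOCF from HeartMan data:** one-sided as written, and drawn from a home device rather than the hospital visit. The direction and size of any bias are unknown.

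The self-care and quality-of-life questionnaires, the other questionnaires given to both arms and the walking distance are collected in both arms and are unaffected. No sample-size figure changes. The point should be corrected, but it does not threaten the primary comparison.

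**What to change.** 1. Relabel wristband calories as a descriptive measure in the intervention arm, with no between-group test and no claim of effect.
2. Ask the medication question in the same way in both arms, at baseline as well as at the end of the study. A question at the end only would leave no baseline for the planned interaction. If both time points cannot be covered, relabel this outcome as intervention-arm descriptive too.
3. For any between-group comparison of heart rate, use only values measured in the same way at the hospital visits in both arms.
4. Remove HeartMan-based LOCF from between-group comparisons. Analyse the observed visit values with a method that handles missing data identically in both arms, for example a likelihood-based mixed model, which assumes data are missing at random.

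The cost is mostly wording, plus one question and a standardised heart-rate reading at visits already planned. The article reports that enrolment was under way at submission, so a baseline answer cannot be recovered for patients already past that visit. The main downside is fewer secondary outcomes on which a between-group effect can be claimed.
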